### Sample processing and testing

All samples for tests which participants receive as standard of care will be transported to Pathology Queensland (Gold Coast University Hospital) for testing according to existing local procedure and policy. For *N. gonorrhoeae* detection by NAAT, all specimens will undergo the combined *Chlamydia trachomatis/ Neisseria gonorrhoeae* test on the Roche Cobas® 4800 machine which is currently used as standard of care by Pathology Queensland. Oropharyngeal and anorectal samples which test positive are confirmed by a secondary Pathology Queensland in-house PCR targeting the gonococcal *opa* genes and *porA* pseudogene [31]. Results from NAAT are reported as *N. gonorrhoeae* “Detected” or “Not detected”. *N. gonorrhoeae* infection is diagnosed only if both the Roche Cobas® 4800 and in-house confirmatory tests are reported as “Detected”. Culture will also be performed for any site which is positive by NAAT for antimicrobial susceptibility testing.

The non-standard of care blood sample for *N. gonorrhoeae-*specific antibody assays will be allowed to clot, then centrifuged at 2,000 x g for 10 min at the Gold Coast Sexual Health Clinic. Serum will be aliquoted into sterile tubes and stored at − 20˚C prior to transport to the Institute for Glycomics, Griffith University for analysis as per standard methods [25, 32–35]. Antibodies in blood-derived serum will be characterised using enzyme-linked immunosorbent assay (ELISA) to quantify the level of specific antibody isotypes that cross-react with *N. gonorrhoeae* whole cell bacteria, and specific target proteins) [25, 32–35]. The ELISA titre is defined as the reciprocal of highest serum dilution with a positive signal (i.e., a signal greater than the negative sample mean plus three standard deviations). The functional activity of antibodies against *N. gonorrhoeae* will be tested in serum bactericidal activity (SBA) and neutrophil-dependent opsonophagocytic activity (OPA) assays [32–35]. Antibody neutralisation of *N. gonorrhoeae* may also be tested in functional assays that measure antibody-dependent blocking of bacterial adherence to epithelial cells or of antigen binding to their ligand [33, 34]. The SBA, OPA or neutralisation titre is defined as the reciprocal of the final serum dilution giving ≥ 50% killing or neutralisation.

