#### Primary outcome

(i)Number of *N*. *gonorrhoeae* infections in participants at any anatomical site over 2 years, diagnosed by nucleic acid amplification test (NAAT).

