### Recruitment and consent

Potentially eligible participants will be identified by clinicians and will be referred to a study investigator who is delegated to provide further information and check eligibility. Eligible participants will be given a Participant Information and Consent Form (PICF) and asked to provide written informed consent prior to commencement in the study. Participants will also consent for the study team to acquire results from other health services for the purpose of the research, to maximise data collection should participants attend for gonorrhoea testing elsewhere during the period of the study. Participants will be able to change or withdraw their consent to participate at any time during the course of the study.

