### Interventions

The MenGo trial involves nine study visits over 24 months for each participant, including a baseline visit (month 0) and 3-monthly follow up visits. Table 2 outlines the trial schema. Participants in the ‘4CMenB vaccine arm’ will receive vaccination at baseline (dose 1) and at month 3 (dose 2). Participants who receive the vaccine will have their blood pressure and temperature taken prior to administration of vaccine. All other physical examinations at all time points will be guided by patient symptoms. At baseline and at each 3-monthly follow up visit, participants in both the ‘4CMenB vaccine arm’ and the ‘no treatment arm’ groups will undergo a sexual health screen as per the Australian STI guidelines [28]. Samples taken will include first-void urine for urogenital gonorrhoea and chlamydia by NAAT, oropharyngeal and anorectal swabs for gonorrhoea and chlamydia by NAAT, and blood for HIV, hepatitis and syphilis screening. Urine and swabs for microscopy examination, *Mycoplasma genitalium* testing and other microbiological culture and sensitivity testing may also be collected. Participants with a positive test will be recalled to the clinic for management and treatment as per standard of care. Participants will continue to receive other standard of care testing and treatment as required. A non-standard-of-care blood sample will be collected from both groups at 3, 6, 12 and 24 months post vaccine for analysis of *N. gonorrhoeae-*specific antibodies.

In order to maximise retention in the study, all participants will receive an automated reminder of their next study visit via the clinic electronic reminder system. Participants will routinely be sent an SMS or email reminder of appointments. Participants who failed to attend will be sent two reminders via SMS or email and a final phone call. Unless a participant is discontinued from the study, study visits, procedures and data can continue to be collected at any time from enrolment up to 24 months (+ 14 days). Reasons for discontinuation include participant withdrawal, adverse event, investigator discretion or termination of the study by the Sponsor. Participants who are lost to follow up during the study period will not be replaced.

**Table 2 Tab2:** Study Schema

Month	0 *	3 *	6 *	9*	12 *	15 *	18 *	21 *	24 *	Un-scheduled
Eligibility	√									
Consent	√									
Randomisation	√									
Vaccination	√	√								
Physical examination (BP, temp)	√	√								

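### The two-test case definition names no site, but the second test is described only for throat and anorectal samples; read literally, urine-only infections drop out of an any-site primary outcome

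*Protocol article*

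**What the plan says.** All places are in the protocol article.

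- **Primary outcome**: the number of "infections in participants at any anatomical site over 2 years", diagnosed by NAAT. Table 1 repeats this, and Statistical methods again refers to NAAT-confirmed infection from any site.
- **Interventions**: the samples at baseline and at each 3-monthly visit include "first-void urine for urogenital gonorrhoea and chlamydia by NAAT", alongside oropharyngeal and anorectal swabs.
- **Sample processing and testing, first test**: all specimens go through the combined "test on the Roche Cobas® 4800 machine which is currently used as standard of care by Pathology Queensland".
- **Same section, second test**: "Oropharyngeal and anorectal samples which test positive are confirmed by a secondary Pathology Queensland in-house PCR". Urine is not named.
- **Same section, case definition**: "infection is diagnosed only if both the Roche Cobas® 4800 and in-house confirmatory tests are reported as" Detected. The sentence carries no limit by site, and no other section gives a separate rule for urine.

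**The concern.** This is the only operational case definition in the article, and it conflicts with the outcome that it serves. Two analysts could follow the same text and count different events. One would accept a urine positive as infection at a urogenital site. The other would reject it because the second test was never run.

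Under the second reading the endpoint narrows to confirmed extragenital gonorrhoea, plus any urogenital infection that happens to accompany it. The Background describes genital infection in men as typically symptomatic and pharyngeal and anal infection as about 90% asymptomatic. The excluded episodes would therefore tend to be the clinically evident ones. Events would also be lost from a small trial.

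**Working it through.** **1. The text, taken step by step for a participant positive only on urine**

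| Step | Source | Result |
|---|---|---|
| Urine collected for NAAT | Interventions | Yes |
| Cobas 4800 run | Sample processing and testing (all specimens) | Detected |
| In-house PCR run | Same section (throat and anorectal positives only) | Not described, so no result |
| Both tests Detected | Same section, case rule | Not met, so not a case |
| Infection at any site by NAAT | Primary outcome, Table 1, Statistical methods | Met, so a case |

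The last two rows disagree. If the same participant also has a throat or anorectal sample positive on both tests, the two rows agree and the participant counts. The conflict is confined to urogenital-only participants or episodes.

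**2. Reproducing the stated sample size**

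Inputs from Sample size: 30% versus 10%, 80% power, significance level 0.05 (sidedness not stated), a proportions test, 56 per group.

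- Exact power of a one-sided Fisher test at 0.05 is 0.794 at 55 per arm and 0.802 at 56 per arm. So 56 is the first size to reach 80%.
- The other variants tried do not give 56 per arm. Two-sided: pooled 62, continuity-corrected 72, unpooled 59, arcsine 60. One-sided: pooled 49, continuity-corrected 58, unpooled 47, arcsine 47.

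The one-sided Fisher calculation is therefore used as the protocol's own basis.

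**3. What the literal rule would cost**

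Let f be the share of infected participants who are positive only at the urogenital site. The article gives no such figure, so f is assumed, and taken as equal in both arms. The countable proportions become 0.30 × (1 − f) and 0.10 × (1 − f). For f = 0.30 these are 0.30 × 0.70 = 0.21 and 0.10 × 0.70 = 0.07.

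| f (assumed) | Control | Vaccine | Expected cases, 56 + 56 | Power, one-sided Fisher | Power, two-sided pooled z |
|---|---|---|---|---|---|
| 0 | 0.300 | 0.100 | 16.8 + 5.6 = 22.4 | 0.802 | 0.761 |
| 5% | 0.285 | 0.095 | 15.96 + 5.32 = 21.3 | 0.777 | 0.733 |
| 10% | 0.270 | 0.090 | 15.12 + 5.04 = 20.2 | 0.749 | 0.703 |
| 20% | 0.240 | 0.080 | 13.44 + 4.48 = 17.9 | 0.686 | 0.640 |
| 30% | 0.210 | 0.070 | 11.76 + 3.92 = 15.7 | 0.615 | 0.571 |

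The ratio of the two proportions stays at 3 in every row (0.30/0.10 = 0.21/0.07). An equal loss in both arms costs precision and does not shift the relative effect.

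**The case against.** The strongest reply is that the sentence should be read with its paragraph. The case rule closely follows the extragenital confirmation step and refers to a confirmatory test, so it presupposes that one was run. The surrounding text sends all specimens through the Cobas and orders culture for any NAAT-positive site, and the outcome sections count any site. The coherent reading limits dual confirmation to the samples that receive it. As to intent, this is probably right. It does not cure the text: a general sentence on how NAAT results are reported stands between the two, the subject of the rule is infection without limit by site, and no rule for urine appears anywhere. Nor is this a detail that the article merely leaves to a fuller document. It states a rule, and that rule conflicts with another one that it states.

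The size is also fairly challenged. The 5% to 30% range is assumed, and nothing in the article narrows it.

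Two stronger readings may tempt a reader, and neither is supported:

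- **That results from other clinics can never count.** Recruitment and consent provides for the team to "acquire results from other health services for the purpose of the research". Nothing says that such samples lack the in-house PCR, since another service could use the same laboratory. How these results are counted can properly be left to the full protocol or analysis plan.
- **That the rule biases the comparison between arms.** It works on laboratory results and does not refer to arm, and Statistical methods assigns the analysis to statisticians who take no other part in the study. The trial is open-label, but uneven application is conjecture.

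**Conclusion.** The case definition is wrong as written. Taken literally, it excludes urogenital-only infections from an outcome that is meant to include them. This rests on the wording alone and does not depend on any assumed figure. It does not show that the investigators intend to exclude urine positives, and it does not reach participants who also have a confirmed extragenital positive.

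The effect on power is illustrative only. It assumes that 5% to 30% of cases are urogenital-only, equally in both arms, with 56 evaluable per arm and true proportions of 30% and 10%. Power would then be 0.777 to 0.615 in place of 0.802. Because the sentence decides what counts as a primary event, it should be settled before events are counted.

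**What to change.** In Sample processing and testing, restrict the two-test requirement to oropharyngeal and anorectal specimens, and state that a urogenital infection is a Cobas 4800 Detected result. State also that cases are classified from laboratory data without reference to arm. The any-site wording in Primary outcome, Table 1 and Statistical methods can then stand as it is.

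A sensitivity analysis limited to dual-confirmed cases is optional.

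The cost is a sentence or two of text. The planned 112, and the target of 130, do not change. The small downside is that urine cases rest on one test, which the optional sensitivity analysis would put in view.

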## Data collection and management

Data collected at each visit will include patient demographics, concurrent medication, previous *N. gonorrhoeae* infections, antibiotic use, sexual behaviour risks and previous STI and blood borne virus (BBV) testing within the last 3 months. If the participant has had testing for *N. gonorrhoeae* elsewhere, all efforts will be made to obtain a copy of those results and associated clinical information either from the patient or directly from the treating physician or clinic. If the participant reports any antibiotic use, the name of the antibiotic and reason for use will also be asked.

### Adverse events

Adverse events (AE) and serious adverse events (SAEs), according to the Common Terminology Criteria for Adverse Events (CTCAE), will be collected from the participant self-reported diary and adverse event enquiry by study investigators at each visit. All SAEs will be reported as per Therapeutic Goods Administration and the Gold Coast Hospital Ethics Committee guidelines.

### Data management

Clinical data and all data in case report forms will be entered into the Sexual Health Information Programme (SHIP) which is the study site’s clinical electronic medical record software, RedCap® and Microsoft Excel. All databases will be stored on a Queensland Health, password protected secure network. Upon consent to participate in the study, the participant will be allocated a study number which will be used to identify the participant throughout the study and retain participant confidentiality. A Master log will be kept for re-identification in the case where participants are required to be re-called for study, safety or clinical reasons. All data will be deidentified for monitoring and audit purposes (by a Study Monitor from the Office of Research, Governance and Development at the Gold Coast University Hospital) and for presentation or publication of results. The Sponsor will also be advised by a Data and Safety Monitoring Committee made up of independent members not involved in the study.

### Statistical methods

Data analysis will be performed by statisticians at the Gold Coast Hospital and Health Service (GCHHS) who are not involved in other study procedures, to reduce chance of bias in the statistical analysis. The number and percentage of participants with NAAT confirmed *N. gonorrhoeae* from any anatomical site will be presented along with 95% confidence interval (CI) at the completion of the study by treatment group. Total observation time will also be recorded. Associations between 4CMenB vaccination status and the incidence of *N. gonorrhoeae* infection will be investigated using Fisher’s exact test and univariate Poisson regression. The incident rate ratio (IRR) with 95% CIs of incidence of *N. gonorrhoeae* infection in the vaccinated group compared to the unvaccinated group will be calculated. Demographic and clinical characteristics of the 4CMenB vaccinated group and the “no vaccine” group will be compared. If any variables are seen to be different between groups (not expected due to randomization) these will be included in a multivariable Poisson regression model along with 4CMenB vaccine predicting *N. gonorrhoeae* infection. The difference in incidence rates of *N. gonorrhoeae* infections between the study treatment and no treatment at the end of the 2-year study period will also be calculated along with 95% CI. The study treatment will be considered effective if the lower limit of the 2-sided 95% CI for the difference between the incidence rates of gonorrhoea in the study treatment group is 30% lower than the no treatment group. Further analyses may be performed based on the observed differences between the treatments in some subgroups. If it is the case that individual participants record more than one incidence of *N. gonorrhoeae* infection in the period of the study, the same analyses will be performed but using a generalized estimating equations (GEE) approach to Poisson regression to account for within participant correlation.

Log(base2) transformed antibody, SBA, OPA and neutralisation titres for each of the 0, 3, 6, 12, and 24-month time points will be, initially, compared between vaccinated and non-vaccinated groups by linear regression with log_2_-titre at time 0 as a covariate. Other clinical and demographic covariates will also be tested, along with vaccination status. Variables will be considered as covariates and retained in the model if P < 0.05. Finally, a mixed effects analysis of the trajectory of the log_2_-titres over the 24-month duration of the study will be performed with participant number as a random effect and vaccination status as the fixed effect of interest. Again, other clinical and demographic variables will be tested as covariates.

The number and percentage of treatment-emergent AEs, study treatment-related AEs, SAEs and AEs leading to study withdrawal will be provided.

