### Sample size

A target of 130 participants will be recruited into the study. To detect a reduction in gonococcal prevalence from 30% (based on a gonococcal prevalence of 29.4% in patients taking PrEP at Gold Coast Sexual Health Service) to 10% (assuming a vaccine efficacy of 30%, based on the predictive MeNZB™ [17]) with 80% power at a significance level of 0.05 using the proportions test, 112 participants will need to be recruited into equal groups of 56 (G*Power 3.1). To account for an attrition or loss to follow up at a rate anticipated to be less than 10% the total recruiting target is 130. The Gold Coast Sexual Health Service see more than 10,000 patients per annum of which approximately 1,700 are GBM, which should enable adequate recruitment to reach the target sample size.

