### Randomisation and allocation

Participants will be randomized 1:1 to 2 groups of 65 – the ‘4CMenB vaccine arm’ or the ‘No vaccine arm’. A biostatistician independent of the clinical researchers will use the ralloc package of Stata 17 (College Station, Tx., USA) to perform block randomization with blocks of size 2–6. Allocations will be placed in sequentially numbered sealed envelopes and kept in a locked cupboard with restricted access to the area (security pass protected). Randomised allocation will only be performed once written informed consent has been obtained. Investigators will allocate study participants from the sequential sealed envelopes, ensuring that there is blinding of the randomisation process.

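### Fisher's exact test is valid but conservative for the participant-level comparison; an exact unconditional test would add about 4 points of power at the planned arm sizes

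*Protocol article*

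**What the plan says.** The Statistical methods section of the protocol article reports, by arm, how many participants had a confirmed infection and what percentage that is. It then states that the association between vaccination and infection "will be investigated using Fisher’s exact test and univariate Poisson regression". Fisher's test is the procedure that fits the infected-or-not comparison. The section does not say whether it is one- or two-sided.

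The same section adds an incidence rate ratio with its confidence interval, and a GEE Poisson model if participants have repeat infections. Its success criterion rests on a different quantity: "The study treatment will be considered effective if the lower limit of the 2-sided 95% CI for the difference between the incidence rates".

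The Sample size section powers only a comparison of proportions, 30% against 10%, "with 80% power at a significance level of 0.05 using the proportions test". It arrives at 56 per arm. Under Randomisation and allocation, "Participants will be randomized 1:1 to 2 groups of 65". Loss to follow-up is expected to stay below 10%.

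**The concern.** Fisher's test treats both margins of the two-by-two table as fixed. In this design only the arm sizes are fixed, and the total number of infected men is random. With arms of about 60 the conditional distribution is coarse, so a nominal 5% test rejects clearly less often than 5% when the vaccine has no effect. It therefore also rejects less often when there is a real effect.

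Boschloo's test ranks tables by the same Fisher p-value but sets the cut-off so that the unconditional error reaches as near to 5% as it can without exceeding it. Its rejection region contains Fisher's, so its power is never lower. In a trial of 130 people, the power of the one comparison that matches the stated sample size is worth keeping if it needs no extra participants or data.

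**Working it through.** **Inputs.** Risks of 30% and 10%, alpha 0.05, 80% power and 56 per arm come from the Sample size section. The 65 per arm comes from Randomisation and allocation. With 10% loss, 65 × 0.9 = 58.5, taken as 58. Two-sided testing is an assumption, in line with the two-sided 95% interval in Statistical methods.

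**Method.** All pairs (x, y) of infected counts in two arms of size n were enumerated.
- Power = Σ over (x, y) in the rejection region of Bin(x; n, p₁) × Bin(y; n, p₂).
- Type I error at common risk π = the same sum with p₁ = p₂ = π.
- Fisher: reject if p_F ≤ 0.05, where p_F sums the hypergeometric probabilities no larger than that of the observed table.
- Boschloo: reject if p_F ≤ c, where c is the largest cut-off whose type I error, maximised over π, is at most 0.05. At 65 per arm c = 0.0716.

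**The plan's own figure.** One-sided Fisher at 0.05 gives power 0.7941 at n = 55 and 0.8025 at n = 56, so it reproduces 56 per arm exactly. The uncorrected two-proportion formula gives 62 (two-sided) or 49 (one-sided). Two-sided Fisher needs 69.

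**True two-sided type I error of Fisher's test.**

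| n per arm | range for π from 0.10 to 0.50 | at π = 0.20 |
|---|---|---|
| 56 | 2.0% to 3.3% | 2.8% |
| 58 | 2.1% to 3.2% | 2.9% |
| 65 | 2.4% to 3.5% | 3.0% |

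At some sizes in between the maximum is a little higher (3.8% at 62), hence about 2% to 4% overall. Boschloo's maximum stays between 4.7% and 5.0%.

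**Two-sided power at 30% versus 10%.**

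| n per arm | Fisher | Boschloo | gain (points) |
|---|---|---|---|
| 56 | 69.4% | 76.0% | 6.7 |
| 58 | 71.6% | 75.6% | 4.0 |
| 60 | 73.0% | 77.4% | 4.4 |
| 62 | 74.9% | 79.2% | 4.3 |
| 65 | 77.5% | 81.7% | 4.1 |

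Gains are taken from unrounded values. From 58 to 65 per arm the gain is 4.0 to 4.5 points.

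**Smaller effect.** The stated 30% efficacy applied to 30% gives 0.30 × (1 − 0.30) = 21%. At 30% versus 21%, power goes from 15.0% to 17.3% at 58 per arm and from 16.4% to 21.1% at 65.

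**Sidedness.** At 56 per arm, moving from one-sided to two-sided Fisher lowers power from 80.25% to 69.35%, which is 10.9 points. If the test is meant to be one-sided, Boschloo still adds about 4 points: 80.25% to 84.2% at 56, and 85.7% to 89.5% at 65.

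**The case against.** Fisher's test is standard and keeps the error at or below 5%. Conditional versus unconditional testing of a two-by-two table is a recognised matter of choice. The primary outcome is the number of infections, and no success criterion uses Fisher's p-value, so changing the test does not change the chance of success under the stated rule. All of this stands, and it limits the point to one of several association analyses.

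A reader might infer that the trial was sized for a less strict test and then analysed with a stricter one. The document does not support that. The Sample size section does not say which proportions test was used, and 56 per arm is what one-sided Fisher gives, while the uncorrected formula does not give it. For the same reason the shortfall from 80% at 56 per arm is mainly a matter of sidedness. Boschloo's test recovers 6.7 of the 10.9 points and still reaches only 76.0%. Two-sided, it passes 80% only from 63 per arm upward, that is, with almost no loss to follow-up.

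A reader might also take the 6.7 points at 56 per arm as the expected gain. That arm size implies more than 10% loss from 65. Within the planned range the gain is about 4 points.

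**Conclusion.** The point holds as a minor, optional improvement. At the planned 58 to 65 per arm, Fisher's test spends about 3% of the allowed 5% at a common risk of 20%. Boschloo's test adds about 4 points of power at 30% versus 10% and never exceeds 5%. With all 65 per arm retained, that moves two-sided power from just below the stated 80% to just above it.

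The result rests on two-sided testing, independent participants, and a simple infected-or-not outcome with equal arms. At 30% versus 21% the gain is 2 to 5 points and no choice of test makes power adequate. It would be wrong to read this as an invalid analysis or as a threat to the trial's decision rule: the Poisson and GEE analyses and the rule on the rate difference are untouched.

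**What to change.** In Statistical methods, for the comparison of the proportion of participants infected, replace Fisher's exact test with Boschloo's exact unconditional test, two-sided at 5%. State this before any analysis; the Data Availability section says that data collection and analysis were not complete at publication.

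The uncorrected two-proportion test should not be used as a substitute. Its maximum type I error at 65 per arm is about 5.3%, so it would replace a test that holds the stated level with one that can exceed it.

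The cost is one phrase in the text, with no extra participants or data. Boschloo's test is less familiar to readers and may need free software outside standard Stata output.

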#### Inclusion criteria

GBM who are:

i.Between 18 and 50 years of age.ii.Able to understand spoken and written English.iii.Men who have sex with other men.iv.Able to participate in study procedures including attending for all study visits.v.At risk of acquisition of gonorrhoea at the time of enrolment into the study.vi.Agree to be contacted via phone/ email by the study team.

AND are:

Currently taking HIV pre-exposure prophylaxis (PrEP) at the time of enrolment ORHave been diagnosed with gonorrhoea in the last 3 months.

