## Discussion

A vaccine to protect against *N. gonorrhoeae* infection is urgently needed due to the rising gonorrhoea case numbers and the continued emergence of antibiotic resistance. Despite more than a century of research, only four gonococcal vaccine candidates have been tested in human clinical trials and none of these elicited protection against gonorrhoea [14]. Failures of these early vaccine candidates created hesitancy in the field and delayed gonococcal vaccine development. However, the field has been reinvigorated by recent epidemiological [17, 19, 20, 36–39] and in vitro data [40] suggesting that meningococcal B vaccines may provide cross protection against gonorrhoea.

MenGO is one of the first randomised control trials worldwide that aims to determine the efficacy of the licenced meningococcal B vaccine 4CMenB against gonorrhoea. The trial includes GBM on PrEP, or GBM with a recent *N. gonorrhoeae* infection. This study is limited to GBM due to the high gonorrhoea incidence in this cohort. In Australia, the majority of *N. gonorrhoeae* infections are in GBM [3], and GBM on PrEP have a gonorrhoea incidence of 37.8 cases per 100-person years [5]. Current guidelines for participants taking PrEP recommend 3-monthly review by a health practitioner for testing for STIs [41]. Therefore, participants are unlikely to bear an excess burden to participate in this study. Recent, prior infection with *N. gonorrhoeae* is a risk factor associated with STI diagnosis [42] and is therefore added as an inclusion criterion.

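### The adjusted gonorrhoea model takes its covariates from chance imbalance between arms instead of a short prespecified list of baseline risk factors, at a modest cost in precision

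*Protocol article*

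**What the plan says.** All of the following is in the protocol article.

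- **Fixed analyses (Statistical methods).** The association between vaccination and "infection will be investigated using Fisher’s exact test and univariate Poisson regression". An IRR with 95% CI and a difference in incidence rates with 95% CI are also promised. None of these depends on observed balance, and the effectiveness criterion is written on the rate difference.
- **Covariate rule (same section).** "Demographic and clinical characteristics of the 4CMenB vaccinated group and the “no vaccine” group will be compared". Then: "If any variables are seen to be different between groups (not expected due to randomization) these will be included" in a multivariable Poisson model alongside vaccination. No variable, threshold or test is named. If participants have more than one infection, the same analyses are repeated by GEE, so the rule carries over.
- **Subgroups (same section).** "Further analyses may be performed based on the observed differences between the treatments in some subgroups". No subgroup is named.
- **Known risk factors.** A man enters by taking PrEP or by having "been diagnosed with gonorrhoea in the last 3 months" (Inclusion criteria). The Discussion says that recent prior infection "is a risk factor associated with STI diagnosis" and gives this as the reason for the criterion. Data collection and management lists "antibiotic use, sexual behaviour risks and previous STI" and blood-borne virus testing among the items recorded at each visit, the baseline visit included.

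**The concern.** The reason to adjust in a randomised trial is that a covariate predicts the outcome. Imbalance is a poor criterion, because with sound allocation it is chance by construction. A rule that waits for imbalance has three consequences:

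1. It can bring in variables that do not predict gonorrhoea.
2. It leaves out strong predictors that happen to balance, although adjusting for them would still reduce residual variation.
3. The content of the model is known only after the data are seen. With no stated precedence, an adjusted and an unadjusted IRR may then stand side by side with nothing to say which one answers the question.

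This is a rule that the article states, not a detail left open for an analysis plan. The subgroup sentence has a related weakness: subgroups picked because their treatment differences stand out will tend to show exaggerated differences.

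**Working it through.** The plan gives no figure of its own on this point, and its sample size is not involved.

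**1. How often would the rule be triggered?** The article gives neither the number of characteristics nor a threshold. Assume k independent characteristics, each tested at p<0.05. Then P(at least one differs) = 1 − 0.95^k.

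| k | P(at least one) |
|---|---|
| 5 | 1 − 0.774 = 23% |
| 10 | 1 − 0.599 = 40% |
| 15 | 1 − 0.463 = 54% |

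So a difference somewhere is quite likely even when randomisation has worked.

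**2. Does the GEE version matter?** At the Discussion's rate of 37.8 per 100 person-years, 65 untreated men followed for two years give 65 × 2 × 0.378 = 49 infections, or 0.76 per man. Repeat infections are to be expected, so the GEE version will probably be used.

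**3. What does the rule gain, and what would prespecification gain?** A simulation of 6,000 trials per setting compared the two.

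- From the article: 65 per arm, 2 years, 0.378 infections per person-year.
- Assumed: eight binary characteristics at 50% prevalence, two of them prognostic with rate ratio 1.5, 2 or 3 each; residual gamma frailty with variance 0.3; the rule triggered at |z| > 1.96.
- Model: Poisson regression with robust standard errors.

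The rule was triggered in 30% to 31% of trials. At a true IRR of 0.7:

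| Covariate rate ratio | SD of log IRR, unadjusted | SD, imbalance rule | SD, prespecified | Variance reduction, prespecified against rule | Power, rule | Power, prespecified |
|---|---|---|---|---|---|---|
| 1.5 | 0.2547 | 0.2551 | 0.2511 | 1 − (0.2511/0.2551)² = 3% | 0.302 | 0.307 |
| 2 | 0.2620 | 0.2607 | 0.2514 | 1 − (0.2514/0.2607)² = 7% | 0.291 | 0.317 |
| 3 | 0.2898 | 0.2854 | 0.2613 | 1 − (0.2613/0.2854)² = 16% | 0.239 | 0.288 |

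The imbalance rule is hardly better than no adjustment. Prespecification gains about 1, 3 and 5 points of power. The smallest gain is no larger than the simulation error of a single power figure, √(0.30 × 0.70/6000) = 0.006.

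**4. Is type I error affected?** At a true IRR of 1.0 the two-sided rejection rate was 0.0525 to 0.054 unadjusted, 0.052 to 0.055 prespecified and 0.048 to 0.053 under the rule. When the more favourable of the unadjusted and rule-based results was taken each time, false claims of benefit ran at 0.027 to 0.028 against a nominal 0.025. With a simulation error of √(0.025 × 0.975/6000) = 0.002, that is no clear inflation.

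**5. Can the data support a fixed model?** At IRR 0.7 with full follow-up, 49 + 0.7 × 49 gives about 83 infections, enough for vaccination plus three covariates.

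**The case against.** The strongest reply is that the main results do not pass through this rule. Fisher's exact test, the univariate Poisson IRR and the rate difference are fixed, and the effectiveness criterion uses the rate difference. A reader might infer that the whole efficacy conclusion depends on chance; the article does not support that. The point is confined to the adjusted model, its GEE version and the subgroups.

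Three other stronger readings also fail:

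- **Adjustment for post-randomisation mediators.** Behaviour and antibiotic use are recorded at every visit and the trial is open label, so a reader might fear this. But the remark that differences are not expected because of randomisation makes sense only for baseline characteristics. The article does not plan such adjustment; it merely omits the word baseline.
- **Unblinded analysts.** The design is open label, but the analysis is given to statisticians with no other role in the study. Whether they know which arm is which is not stated.
- **Entry route left uncontrolled.** No stratification is described, but randomisation balances entry route in expectation, and the rule itself would pick it up if it were imbalanced.

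It is also fair to say that the sizes rest on assumed inputs. The article gives no count of characteristics, no threshold and no covariate effects. The two entry routes can overlap and their mix is not given; if nearly all men take PrEP, PrEP use will explain little. The subgroup sentence is permissive, and no claim or decision hangs on it.

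What stands after all this is the selection criterion itself, and the silence on which IRR takes precedence.

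**Conclusion.** The point holds as a modest defect that is cheap to correct. The existence and content of the adjusted IRR are largely a matter of chance, the rule gains almost nothing over no adjustment, and the article's own named risk factor enters only if it happens to be imbalanced.

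The cost is precision and clarity, not type I error. At IRR 0.7 it amounts to roughly 3% to 16% of the variance of the log IRR and about 1 to 5 points of power. These figures assume two prognostic covariates with rate ratios of 1.5 to 3, and the gain is small if real predictors are weak.

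An IRR of 0.7 is the relevant setting: the Background cites efficacy of 31% to 40% for the two vaccines and the Sample size section names 30%, which correspond to IRRs of about 0.6 to 0.7. A stronger assumed effect, such as IRR 0.5, can make the power gain look larger, but it goes beyond those efficacy figures. The 30% to 10% contrast used for sample size does imply a larger effect, 1 − 10/30 = 67%, but that conflicts with the 30% stated beside it and is a separate matter.

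**What to change.** Replace the imbalance rule in Statistical methods with wording along these lines:

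> The adjusted Poisson model, fitted by GEE where infections recur, includes gonorrhoea in the last 3 months, PrEP use and one named sexual-risk measure, all taken at month 0, whatever their observed balance. Only baseline values are used for adjustment.

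State which IRR, adjusted or unadjusted, is primary and which is supportive. Baseline characteristics can still be tabulated by arm, but the table should not determine the model.

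As a secondary change, replace the subgroup sentence with one prespecified subgroup, entry route, tested by interaction and labelled exploratory.

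The cost is a change of wording, best made before outcome data are compared by arm. The covariates are already collected at the baseline visit, and neither the sample size nor any study procedure changes. The one decision needed is which sexual-risk measure to name.
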